#### Glycemic and Blood Pressure Control Targets

The following indices will be used to determine whether participants are meeting treatment goals. These goals conform to current standard of care in outpatient diabetes management.

• Fasting/pre-prandial Blood Glucose:          < 110 mg/dl (range 70-109 mg/dl)

• Bedtime Blood Glucose:                            < 130 mg/dl (range 70-129 mg/dl)

• Two-hour post-prandial Blood Glucose:    < 140 mg/dl (range 110-139 mg/dl)

• HgbA1C target:                                        < 7.0%

• Blood pressure                                        < 130/80 mmHg

#### Role of the Case Manager

The case manager is to serve as an adjunct to usual care by providing more frequent contact between the patient and his/her health care provider. This will be accomplished through: (1) Real time tracking of patient-generated blood glucose and blood pressure data using the FORA 2-in-1 and Telehealth System for diabetes; (2) Minimum of monthly phone calls to participants to reinforce diabetes self-management behaviors, e.g. medication compliance, blood glucose monitoring, diet/exercise programs; (3) More frequent phone calls as needed for patients undergoing active changes in management; (4) Telephone reminders about upcoming scheduled appointments; and (5) Use of uploaded blood glucose and blood pressure data and information obtained from participant contact to determine need for additional interventions. The case manager will function as liaison between the primary provider and the participant, identifying those participants in need of additional intervention and facilitating implementation of a revised treatment plan.

#### Case Manager Telephone Follow-up

The nurse case manager will be responsible for conducting regular follow-up by telephone with all TACM intervention participants. The initial phone follow-up will occur within two weeks of the initial study visit. Thereafter, the minimum frequency of phone follow-up will be monthly for participants who are meeting treatment targets based upon weekly review of uploaded data. More frequent contact is permitted for participants not meeting treatment targets and in whom active interventions are ongoing. Routine follow-up calls will review the following: (1) Interval health-related events and changes in medications; (2) Current level of glycemic and blood pressure control, based on data logged in the FORA system; (3) Frequency and severity of hypoglycemia on the current therapy based on both FORA system data and patient perception of hypoglycemia; (4) Reinforce adherence with diet/exercise program and medications; (5) Reinforce participant education relating to caring for diabetes, treatment of hyper/hypoglycemia and safe driving rules; (6) Remind participants about upcoming scheduled appointments with their primary provider and/or study visits; and (7) Answer participants' questions.

#### Usual Care Group

Apart from study visits, participants will be followed by their Franklin C. Fetter PCPs. The provider will be responsible for determining treatment parameters, making changes in the treatment regimen, and determining the timing of follow up visits. Between scheduled office encounters, contact between participant and provider will be patient initiated. The provider may use clinic nurses to follow up on problematic patients or patients with abnormal results. In essence, this group will receive the current standard of care at the study clinics.

### Study Instruments and Data Collection Schedule

See Figure 4 and Tables 1 and 2, for the study design and study flow, data collection schedule, and data collection measures and instruments, respectively.

**Figure 4 F4:**
[figure not shown]
**Description of Study Design and Study Flow**.

**Table 2 T2:** Data Collection Measures and Instruments

Measure	Data Collected	Method
**Primary Outcome**	Hemoglobin A1c	Blood specimens will be obtained at baseline, 3-, and 6-months visits.

**Secondary Outcomes**	Blood Pressure	Blood pressure readings will be obtained at baseline, 3-, and 6-months visits.

	Quality of life	Quality of life will be measured by the SF-12 [31], which is a valid and reliable instrument to measure functional status.

		

**Process Measures**	Information	This will be measured by the 24-item Diabetes Knowledge Questionnaire (DKQ) [32]

	Motivation	This will be measured with the 12-item Diabetes Fatalism Scales (DFS) [33].

	Self-Efficacy	This will be measured by the perceived diabetes self-management scale (PDSMS) [34].

	Behavioral Skills	This will be assessed with the Summary of Diabetes Self-Care Activities (SDSCA) scale [35].

	Medication Adherence	This will be measured with the new 8-item self-report Morisky Medication Adherence Scale (MMAS) [36].

		

**Self-report measures**	Demographics	Previously validated items from the 2002 National Health Interview Survey [37] will be used to capture age, gender, race/ethnicity, marital status, household income, and health insurance.

	Social support	The Medical Outcomes Study (MOS) Social Support Survey [38] will be used to measure social support.

	Health Literacy	The abbreviated version of the Test of Functional Health Literacy in Adults (S-TOFHLA) [39] is designed to rapidly screen patients for potential health literacy problems.

	Depression	The PHQ-9 is a brief questionnaire that scores each of the 9 DSM-IV criteria for depression [40].

	Medical Comorbidity	The patient's history of medical comorbidity will be documented using a standardized and validated questionnaire [41].

	Service Delivery Perceptions	This will be assessed with 5 items that have been previously validated in mental health studies. The items were slightly modified to be relevant to diabetes.

	Treatment Credibility	To assess for differences in outcome expectancy, a modified treatment credibility scale developed by Borkovec and Nau (1972) will be used [42].

	Resource Utilization & Cost	The perspective of cost will be that of the payer. Previously validated questions on resource utilization will be administered as a part of the baseline, 3-, and 6-month visits.

### Intervention Delivery, Treatment Integrity, and Treatment Adherence

A full-time registered nurse (RN) will conduct the screening, patient scheduling, consent, and enrollment procedures as well as deliver the case management intervention. A blinded research assistant (RA) will conduct all study assessments. A data coordinator will enter all study related data into a secure web-based data system and perform all related data tracking and coordination duties.

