### Location and Setting

This study will be conducted primarily in eight community-based adult medicine primary care practices within the Franklin C. Fetter Family Health Center, Inc. Additional practices will be added if adequate sample is not obtained from the primary target practices. The Franklin C. Fetter Family Health Center, Inc. is a FQHC with eight adult medicine primary care clinics, 1 pediatric primary care clinic, a home health program, and two pharmacy locations. The clinics provide service to residents in Berkeley, Charleston, and Dorchester Counties of South Carolina. Demographic characteristics of the clinic population are as follows: 70% African American, 25% White, 5% Hispanic/other, 70% with income below 100% of federal poverty level, and 46% uninsured. The structure of each site is similar with the same number of practitioners and staff.

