### Randomization

All participants are randomly assigned to one of the two study arms (n = 100 per arm). The study coordinator will verify all eligibility criteria prior to randomization. The procedure and risks will be explained to the participants and the consent form signed as per standard clinical practice. All participants are randomly assigned to either the intervention (TACM) (n = 100) or usual care (UC) (n = 100) groups. Randomization takes place in waves, with approximately 50 subjects randomized every 6 months. The randomization sequence is generated by the research team biostatistician using a permuted block randomization scheme stratified by clinic site. The randomized assignment for eligible participants is accessible to the study coordinator using an envelope-based system at each clinic site. Once a randomization assignment is provided, the participant is entered into the study and will be included in the intention to treat analysis in accordance with the CONSORT guidelines [26].

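### The nurse who delivers TACM also recruits, and with permuted blocks within clinic she can guess the next assignment better than chance

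*Protocol article*

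**What the plan says.** The relevant statements are spread over several sections of the Protocol article.

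- **Intervention Delivery, Treatment Integrity, and Treatment Adherence:** one member of staff holds both roles: "A full-time registered nurse (RN) will conduct the screening, patient scheduling, consent, and enrollment procedures as well as deliver the case management intervention". The same section gives study assessments to a blinded research assistant and data entry to a data coordinator.
- **Case Manager Telephone Follow-up:** the nurse case manager telephones every TACM participant regularly.
- **Randomization:** the biostatistician generates the sequence "using a permuted block randomization scheme stratified by clinic site", with 100 participants per arm. No block size is given. Assignments are "accessible to the study coordinator using an envelope-based system at each clinic site". Before that, "The study coordinator will verify all eligibility criteria prior to randomization". Randomization proceeds in waves of about 50 every six months, and a participant enters the study once an assignment is given.
- **Location and Setting:** recruitment is mainly from "eight community-based adult medicine primary care practices".
- **Trial Population and Recruitment:** candidates come from billing records with physician permission, or from referrals to research assistants. Consent and screening are ascribed to research staff in general.

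**The concern.** Allocation is concealed only if the person deciding whether and when to enrol a patient cannot foresee the arm. Here the recruiter is unblinded and delivers one of the two arms, so she learns each TACM assignment as part of her work. Permuted blocks within clinic force the arms back into balance in each small stratum, so past assignments carry information about the next one. She does not need to see inside an envelope to use it.

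The intervention asks for daily testing and uploading, and the nurse's own delivery is reviewed for fidelity. A recruiter in that position could, even without intending to, schedule or encourage motivated patients when TACM is likely and postpone others. The arms would then differ in prognosis at entry. HbA1c is an objective measure and the assessor is blinded, but both safeguards act after allocation and leave this route open.

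**Working it through.** **The plan's own figures.** The article states no figure for predictability of allocation, so there is none to reproduce. Its power statement is unaffected by this point.

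**Inputs.** Allocation is 1:1 with 200 participants and eight clinics. An even spread (assumption) gives 200 / 8 = 25 per clinic. Block size is not stated, so sizes 2 to 10 are shown.

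**Guessing rule.** Guess the arm with fewer assignments so far in that clinic, and toss a coin when they are equal. Each completed block is balanced, so the running difference in a clinic equals the difference within the current block. The rule therefore needs no knowledge of block size or block boundaries.

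**By hand, block of 4.** Probability of a correct guess at each position:

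- Position 1: 1/2.
- Position 2: two of the three remaining places belong to the other arm, so 2/3.
- Position 3: the first two assignments are equal with probability 1/3, and the third is then forced. Otherwise it is a coin toss. So 1/3 × 1 + 2/3 × 1/2 = 2/3.
- Position 4: 1.

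The mean is (1/2 + 2/3 + 2/3 + 1) / 4 = 17/24 = 0.708.

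**All sizes.** The second column enumerates every sequence in a complete block. The third simulates 25 participants in a clinic, where the last block may be incomplete.

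| Block size | Complete blocks | 25 per clinic |
|---|---|---|
| 2 | 75% | 74% |
| 4 | 71% | 70% |
| 6 | 68% | 68% |
| 8 | 67% | 66% |
| 10 | 65% | 63% |

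Check for size 2: twelve complete blocks and one extra participant give (12 × 1.5 + 0.5) / 25 = 0.74.

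**Mixed block sizes, 25 per clinic, guesser ignorant of the sizes.** Sizes 2 and 4 give 71%; 4 and 6 give 68%; 2, 4 and 6 give 69%; 4, 6 and 8 give 67%.

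**Reading.** The overall range is 63% to 75%. Over 200 participants that is 0.63 × 200 = 126 to 0.75 × 200 = 150 correct guesses, where chance gives 100. A recruiter with no knowledge of past assignments stays at 50%.

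**The case against.** **She is not the only gatekeeper.** Billing-record identification, physician permission, referrals to research assistants, consent by research staff and a coordinator's eligibility check all involve other people, and the HbA1c threshold of 8% limits discretion. This stands in part: it narrows her influence and shows that the sections need reconciling. It does not withdraw the explicit statement that the nurse screens, schedules, consents and enrols. The staffing section lists no study coordinator, so the text does not show that this role is independent of hers.

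**Safeguards may be in the full protocol.** Varying blocks and sealed, opaque envelopes are details that an article may leave out, and their absence is no finding. But mixed blocks still allow about 67% to 71% correct guesses, and opaque envelopes do not hide assignments she already knows.

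**Randomization is in waves.** If a whole wave were enrolled before any of it was randomized, prediction would matter less. The article does not say so; entering each participant once an assignment is given reads as sequential.

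**Stronger readings that the article does not support.** A reader might infer that part of the sequence is known outright. For a block of size 2b, a share 1/(b+1) of assignments is certain (one third for blocks of 4), but only if the size is fixed and she knows it, and neither is stated. A reader might also want to put a size on the bias in HbA1c. That needs a prognostic difference between patients steered to each arm, for which the article has no source. Nor is it right that analysis can do nothing: the mixed model uses baseline HbA1c and adjusts for age, race, gender, comorbidity, social support, health literacy and depression, which would remove part of any selection. Selection on what the recruiter perceives but nobody records would remain.

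**Conclusion.** The point holds as an avoidable risk of selection bias at enrolment, built into the stated roles. It is not evidence that bias will occur, and its effect on the HbA1c comparison cannot be quantified from the article. What can be quantified is predictability: about 63% to 75% correct guesses for block sizes 2 to 10, and 67% to 71% for the mixed sizes examined. This assumes that the nurse carries out the roles as written, that assignments are made one at a time, and, for the simulated figures, that participants are spread evenly over eight clinics.

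It should be fixed before recruitment, since later analysis can repair it only in part. The change is small for what it protects.

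**What to change.** 1. In the section on intervention delivery, give screening, consent and enrolment to existing staff who neither deliver TACM nor know past allocations. The blinded research assistant, acting before allocation, is one possibility, provided someone else handles the assignment. Bring Trial Population and Recruitment and Randomization into line, so that each task has one named role.
2. In Randomization, replace on-site envelopes with central release, either through the existing web-based system if it can support this (the article describes it only for data entry) or by the biostatistician. Release an assignment only after consent, eligibility and baseline data are locked.
3. Do not move enrolment to the coordinator who accesses the assignments, because that person could predict in the same way.
4. Treat mixed block sizes as a supplement. Neither they nor central release alone stops a recruiter who knows past assignments from guessing; separating the roles is the essential step.

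The cost is some research assistant time and modest system set-up. Sample size, outcome schedule and analysis model stay as they are.

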## Methods

The study is a 2 group randomized controlled trial with randomization of individual participants, blinded outcomes assessments at baseline, 3-months, and 6-months, and concurrent economic evaluation.

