**Self-Report Measures**			

Patient Demographics	X		

Social support	X		

Health Literacy	X		

Depression (PHQ-9)	X		

Medical Comorbidity (Charlson Index)	X		

Service Delivery Perceptions/Treatment Credibility			X

Resource Use	X	X	X

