### Primary Outcome Measure

The primary outcome is HbA1c level at 6 months of follow-up.

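### Treatment credibility is collected only at 6 months, too late to measure outcome expectancy, and routing it and other arm-related items through the blinded assessor puts the blinding at risk, mainly for blood pressure

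*Protocol article*

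**What the plan says.** The opening of the Methods section describes "blinded outcomes assessments at baseline, 3-months, and 6-months". The section on intervention delivery, treatment integrity and treatment adherence says who does this: "A blinded research assistant (RA) will conduct all study assessments". It states no exception. The same section gives case management to a registered nurse and data entry to a data coordinator.

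Table 1 has a row "Service Delivery Perceptions/Treatment Credibility" with its only mark in the 6-month column. HbA1c, blood pressure and SF-12 are also due at that visit. Resource use is marked at baseline, 3 months and 6 months.

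Table 2 gives the purpose of the credibility scale: "To assess for differences in outcome expectancy, a modified treatment credibility scale". On service-delivery perceptions it says: "This will be assessed with 5 items that have been previously validated in mental health studies", with slight modification for diabetes. On the secondary outcomes it says "Blood pressure readings will be obtained at baseline, 3-, and 6-months visits" and "Quality of life will be measured by the SF-12". The article does not give item wording, the order of procedures within a visit, or whether questionnaires are read out or self-completed.

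**The concern.** There are two faults in how these items are placed.

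The first is timing. Expectancy is what a participant thinks the allocated treatment will do. It has to be recorded once the allocation is known and before the treatment has had time to work. A first reading at 6 months cannot separate a participant who expected to do well from one who did well and now finds the treatment credible. A difference between arms could then be a cause of the outcome, a consequence of it, or both.

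The second is who hears the answers. The arms differ in ways a participant is likely to mention when asked about treatment or service: a home device with daily uploads and nurse telephone calls in one, ordinary clinic care in the other. If the assessor learns the arm from such answers, later measurements by that assessor are no longer blinded. Blood pressure is a named secondary outcome and, on the stated staffing, the assessor takes it.

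**Working it through.** No formula is needed for the main point; the passages are set side by side.

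**Timing of credibility**

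1. Purpose (Table 2): to see whether expectation of benefit differs between arms.
2. Timing (Table 1): 6 months only, with no mark at baseline or 3 months.
3. The primary endpoint falls at the same time: "The primary outcome is HbA1c level at 6 months of follow-up". The expectancy score is therefore taken when the outcome is due, after the full intervention period.
4. Who supplies a score: only those who attend the 6-month visit. The sample-size section raises 80 per arm to 100 per arm, and 80 / (1 − 0.20) = 100 reproduces this. The allowance is 100 − 80 = 20 per arm, or 40 of 200. The article assigns it to dilution under intention to treat together with early dropout. If all of it were dropout (an assumption, and the upper end of that allowance), 40 participants would have no score. If none were, the score would be complete but still taken too late.

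Steps 1 to 3 conflict whatever the item wording, mode or order of administration. A fuller protocol could resolve the conflict only by changing the published schedule.

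**Route to the assessor**

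1. All assessments go to the blinded research assistant, so blood pressure and the arm-related items go to the same person.
2. At 6 months, the service-delivery and credibility items share a visit with blood pressure and SF-12. For the blind to be lost before these are recorded, three things must all happen: the answers disclose the arm, the assistant hears or sees them, and this comes before the measurement. The article settles none of the three.
3. At 3 months only the resource-use questions (and perhaps the repeated self-care scale) could disclose the arm. Table 2 describes the resource questions as administered within the baseline, 3- and 6-month visits. If an assistant learned the arm at 3 months, the 6-month blood pressure could be affected even if the 6-month visit were ordered with care.

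**Outcome by outcome**

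- HbA1c comes from a blood specimen and is little affected by what the assistant knows.
- SF-12 is reported by participants who know their arm, so blinding the assistant protects it only in part.
- Blood pressure is the outcome for which the assistant's blinding matters most.

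**The case against.** The strongest objection is that the blinding has not been shown to break. Both tables list the credibility and service-delivery items under self-report measures, after the outcomes. That is compatible with self-completion at the end of the visit, although it does not establish it. If these items do come last at the final visit, the outcomes are already recorded. Order and mode of administration are details that a condensed article may leave to the full protocol. This stands. A reader might infer from the word all in the staffing sentence that the 6-month blood pressure and SF-12 are unblinded. The article does not support that; it supports only a risk with no described safeguard.

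The contrast between arms can also be overdrawn. The Rationale lists glucose monitoring among the usual-care patient's own duties, and the Usual Care Group section allows providers to use clinic nurses for follow-up. Mention of testing or of a nurse therefore need not identify the arm, and it would be wrong to say that only one arm sees its glucose values. This stands too, and it weakens the 3-month route in particular.

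A reader might also want to size the observer bias against the 3.4 mm Hg systolic difference quoted in the Background. That figure is another trial's result, and any observer shift set against it would be a guess. The article gives neither a blood pressure standard deviation nor a measurement method.

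Finally, neither the Statistical Analysis Plan section nor the Exploratory analyses section names an analysis of the credibility score, so no stated conclusion depends on it. That limits the damage. It does not remove the mismatch between purpose and timing.

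**Conclusion.** The timing fault is established from the article alone. A scale meant to measure expectancy is collected only after six months of treatment and only from attenders, so it cannot do what Table 2 says it is for. The loss is the ability to say whether expectation of benefit differed between arms. The primary analysis does not depend on it.

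The blinding point holds as a risk. It assumes that answers about treatment, service or resource use can disclose the arm and that the assistant collects them in person, which is the plain reading of the staffing sentence but is not spelled out. It bears mainly on blood pressure, less on SF-12, and hardly on HbA1c. Its size cannot be given. The change is still worth making, because it is cheap and blood pressure is a named secondary outcome.

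**What to change.** 1. Collect treatment credibility on a short self-completed form immediately after the allocation is disclosed, and keep the form from the blinded research assistant. A 6-month repeat may stay if it is labelled as satisfaction and not as expectancy.
2. At each follow-up visit, take blood and blood pressure before any questionnaire.
3. Have the service-delivery, credibility and resource-use items self-completed last and returned in a sealed envelope to the data coordinator. Do this at 3 months (resource use) as well as at 6 months, since what the assistant learns at 3 months may be remembered.
4. Amend Table 1 and the staffing sentence to match.

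The cost is a change to the schedule and visit procedure and one short form at allocation. No extra participants or staff are needed. The downside is that some participants with low literacy will need reading help. This should come from existing staff other than the blinded research assistant and the nurse case manager, because the nurse would be hearing answers about her own service. The data coordinator is one possibility.
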